#### 2.6.4. Mental Health Clinician Provision of Preventive Care

In the baseline and follow-up online surveys, staff will report, for each of the risk behaviours, the proportion of their clients who had risk behaviours documented in their care plan and with whom the clinician had a conversation about referral services. Staff will also indicate (on a 5-point Likert scale) how regularly they: check in with clients about their progress in achieving behaviour change goals, check in with clients about their uptake of referral services, and update the care plan as clients progress. Clinicians will report if their opportunity to provide preventive care was impacted by COVID-19.

#### 2.6.5. Implementation Process Outcomes

In the follow-up online survey, staff of intervention services will report the perceived intervention acceptability, appropriateness, and feasibility using validated measures [55]. The delivery and uptake of the implementation strategies will be measured in project logs recorded by the research team/implementation support officers and HCCs, including advisory group meetings held, employment of HCC, implementation support provision (number and mode of interactions), participation of staff in training, provision of audit and feedback summaries, and provision of client resources. Adaptations made to the intervention, including in response to COVID-19 (e.g., constraints on face-to-face service delivery) will be assessed and recorded by the project team in monthly meetings. To capture aspects of the model of care, delivery of the ‘healthy choices’ consultation will be recorded by the HCC using an electronic template (e.g., number of appointments held, provision of care elements, and client risks and goals set). Content within clinical review meetings relating to preventive care will be assessed (likely by the HCC).

#### 2.6.6. Cost Data

The resources required to develop and implement the model of care will be prospectively collected during the intervention period in project logs, such as training for staff, modification of service electronic tools, and resources required to deliver the healthy choices consultation (e.g., HCC salary). In the online staff survey (baseline and follow-up), staff will report professional discipline, role and hours worked per week to valuation of their time. Staff will also report how frequently they provided preventive care and the average time taken to provide preventive care to an individual client.

### 2.7. Sample Size and Power

An average of 120 eligible clients per service will be randomly selected from service records during both the pre- and post-implementation periods (720 intervention group; 720 control group). An estimated 25% of selected clients will consent and complete the interviews, with a total of 360 clients at each time point (180 intervention group; 180 control group). Assuming an intraclass correlation of 0.05 (to adjust for clustering) and a baseline prevalence of 20% [28], this sample size will provide 80% power to detect at least a 25% absolute increase in the primary practice change outcomes, with a type 1 error rate of 0.017 to account for multiple testing.

For the cohort follow-up, it was estimated that 60% [55] of the 200 randomly selected participants will complete the cohort follow-up survey, providing a sample of 120 (*n* = 60 in each group).

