### 2.2. Randomisation and Blinding

Twelve services will take part in the study. Based on the number of services available in each LHD, this will include six from one LHD, three from the second, and three from the third. An independent statistician will use a computerised random number function to randomly allocate services in a 1:1 ratio to either the intervention or control condition within the strata (three LHDs). Constrained randomisation will be used to ensure balance between the intervention and control groups in terms of service characteristics: size (based on client numbers; 2 levels; cut off point of 1500), structure (2 levels: single site versus multisite), and rurality (determined by service postcode; 2 levels: major city vs. inner/outer regional [40]). Following the randomisation, researchers, services, clinicians, and clients will not be blind to allocation. Statisticians undertaking outcome analyses will be blinded to group allocation. Interviewers collecting data from clients will be blinded to group allocation (with the exception of the end of the follow-up survey where intervention participants will be asked additional questions regarding the intervention).

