### 2.8. Analysis

Mixed effects logistic regression models will compare the primary outcomes and secondary practice change outcomes (preventive care receipt) between the intervention and control groups at the post-implementation follow-up, adjusting for clustering by service with a service level random intercept. The models will also adjust for potential confounders, including baseline prevalence of preventive care, age, gender, psychiatric diagnosis, and length of time in treatment, as well as LHD as fixed effects. Analyses will be carried out on an intention to treat basis.

In the cohort sub-study, generalised mixed effects regression models will determine the change over time (baseline to 9-month cohort follow-up) in the intervention compared to control participants in the measures relating to client behaviour change: smoking status (yes/no), serves of vegetables per day, serves of fruit per day, number of standard alcohol drinks per week, minutes of moderate and vigorous physical activity per week and body mass index (BMI). Models will adjust for clustering by service and potential confounders as well as LHD. Descriptive analyses will be used to report the remaining measures.

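### The stated 80% power makes no allowance for having only 12 services: with a two-sided t reference and no credit for covariate adjustment it is about 61–69%, and 80% needs about 28–30 points

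*Protocol article*

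**What the plan says.** The design is set out in section 2.2: "Twelve services will take part in the study", and an independent statistician will "randomly allocate services in a 1:1 ratio to either the intervention or control condition within the strata (three LHDs"). The three districts contribute six, three and three services.

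Section 2.7 gives the inputs to the power statement:
- Response: "An estimated 25% of selected clients will consent and complete the interviews". Of the 720 selected in each arm, that leaves 180 interviewed per arm at each survey.
- Clustering: "Assuming an intraclass correlation of 0.05 (to adjust for clustering").
- Control rate: "a baseline prevalence of 20"%.
- Type 1 error rate: 0.017, set for multiple testing. Sidedness is not stated.
- Conclusion: "this sample size will provide 80% power to detect at least a 25% absolute increase in the primary practice change outcomes".

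Section 2.8 analyses the primary outcomes with mixed effects logistic regression, "adjusting for clustering by service with a service level random intercept". District enters as a fixed effect, and baseline prevalence of preventive care is among the adjustment variables. Neither section mentions degrees of freedom or a reference distribution for the treatment effect.

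**The concern.** Treatment is allocated to services, so the treatment effect is a between-service comparison with six services on each side. The design effect inflates the variance for clustering, but it does not allow for that variance being estimated from 12 units. The usual allowance is a t reference with between-service degrees of freedom. The adjustment is large here because the 0.017 threshold lies far into the tail: the two-sided critical value rises from 2.39 to 2.86 with 10 df and to 3.00 with 8 df.

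All three primary outcomes rest on this one calculation. If the analysis uses a valid small-sample test, a null result would be read as coming from a trial with 80% power when the power may have been nearer 60–70%. If it does not, the 0.017 level chosen to protect three tests would not hold.

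**Working it through.** **Inputs.** 12 services, 6 per arm (2.2). 180 completed interviews per arm (2.7), so 180/6 = 30 per service, taken as equal. ICC 0.05, rates 20% and 45%, α = 0.017 (2.7), assumed two-sided.

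**Reproducing the stated figure**
- Design effect = 1 + (30 − 1) × 0.05 = 2.45.
- Effective n = 180/2.45 = 73.5 per arm.
- SE = √[(0.20 × 0.80 + 0.45 × 0.55)/73.5] = √(0.4075/73.5) = 0.0745.
- Noncentrality = 0.25/0.0745 = 3.36.
- Normal critical value at two-sided 0.017 = 2.387.
- Power = Φ(3.36 − 2.387) = 83%. With pooled variance under the null it is 81%, and by arcsine 82%.

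So the stated 80% is reproduced to within a few points by the two-sided normal formula.

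**Same inputs, t reference (noncentral t, no covariate credit)**

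| Between-service df | Critical value | Noncentrality | Power |
|---|---|---|---|
| 10 (12 services − 2 arms) | 2.859 | 3.36 | 69% |
| 8 (also − 2 for district) | 3.003 | 3.36 | 64% |
| 8, with 6/3/3 strata | 3.003 | 3.26 | 61% |

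The third row allows for the two districts of three services, which can only split 2:1. The information is 1.5 + 2/3 + 2/3 = 2.83 against 3.0, so the noncentrality becomes 3.36 × √(2.83/3.0) = 3.26.

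**Detectable difference at 80% power from 20%.** About 28 points with 10 df, and about 30 points with 8 df.

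**Simulation.** For 12 services of 30 clients with ICC 0.05, a t-test on service counts had 67% power. The mixed logistic model with t critical values had 73% (10 df) and 74% (8 df). The model figures are slightly flattering, because its null rejection rate was still about 1.8–2.5% against 1.7%.

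**Credit for baseline prevalence.** Let c be the correlation between a service's true baseline and follow-up rates. The article does not give c, so a range is shown. With 30 clients at each survey, the observed service rates correlate at r = c × (30 × 0.05)/2.45 = 0.612c, and the noncentrality becomes 3.36/√(1 − r²).

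| c | r | Noncentrality | Power, 7 to 9 df |
|---|---|---|---|
| 0.5 | 0.31 | 3.53 | 66–72% |
| 0.8 | 0.49 | 3.85 | 75–80% |
| 1.0 | 0.61 | 4.25 | 83–88% |

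With 7 df and the 6/3/3 strata loss as well, c = 0.8 gives 72% and c = 1.0 gives 81%.

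**Error rate if an uncorrected z were used.** Referring a t statistic to 2.387 gives a two-sided error of 3.8% (10 df), 4.4% (8 df) or 4.8% (7 df). Simulated null rejection of the Wald z test in the mixed logistic model was 4.2–4.7% with arm only and 6.6–7.1% with district added. With baseline prevalence also added it was 6.4–8.0%.

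**The case against.** **The sum is not wrong.** This is fair. The inputs do yield about 80% under the standard design-effect formula. The fault is the reference distribution, which does not suit 12 services.

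**The planned analysis may recover the loss.** This stands in part. Section 2.8 does adjust for baseline prevalence, and with c at 0.8 or above power is about 75–80% or more. District might also explain some between-service variance; with 8 df and the strata loss, an assumed 36% explained would give about 74% and 50% about 79%. A reader might infer that the trial cannot reach 80% under any valid test, and the documents do not support that. But section 2.7 credits neither adjustment and gives no correlation, so its figure does not rest on them.

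**The ICC is itself a guess.** True in both directions: with t and 7 to 10 df, power is 74–81% at 0.03 and 47–54% at 0.08. The claim has to hold at the 0.05 the protocol chose.

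**Sidedness is not stated.** If 0.017 were one-sided, t would give 80% with 10 df (critical value 2.454) and 75–77% with 8 df (2.553). Nothing in the article indicates one-sided testing, so two-sided is assumed here.

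**The test is not specified.** This stands. A reader might infer that the trial will run at a 4–7% error rate. Section 2.8 names a model, not a Wald z test, and a separate analysis plan may contain a small-sample correction. The error figure is therefore conditional. The power point does not depend on it.

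**Conclusion.** The concern holds for the power statement in section 2.7. For a two-sided 0.017 test, the stated 80% comes from a normal critical value that ignores how few services there are. On the article's own inputs and without covariate credit, power for 20% to 45% is about 69% (10 df) or 61–64% (8 df), and 80% power corresponds to about 28–30 points. Baseline adjustment could restore about 75–80% or more if service rates are strongly correlated over time (about 0.8 or higher), an assumption that section 2.7 does not make.

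The inflated error rate of about 4–7% per outcome is a conditional risk, not a feature of the plan as written.

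These figures assume two-sided testing, 30 clients in every service and an ICC of exactly 0.05. Section 2.3.2 gives only an average number selected per service, and unequal sizes would lower power further.

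**What to change.** In section 2.7, do one of the following:
- Restate the power as about 60–70% for a 25-point increase, or 80% for about 28–30 points, without adjustment credit.
- Keep 80% for 25 points, and state the baseline-to-follow-up correlation of service rates under which baseline adjustment delivers it.

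In either case, say whether 0.017 is two-sided.

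In section 2.8, or by reference to the analysis plan if it already covers this, refer the treatment effect to a t distribution with between-service degrees of freedom (services minus service-level parameters) or an equivalent small-sample correction, so that the 0.017 level holds.

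The cost is a less favourable stated power and a standard software option. No extra services or clients are required.

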#### 2.6.1. Primary Trial Outcomes

The primary outcomes are the proportion of clients who reported receiving elements of the AAR framework of preventive care: (1) assessment for all chronic disease risk behaviours (tobacco smoking, inadequate fruit and vegetable consumption, harmful alcohol use and physical inactivity), (2) brief advice for all relevant risk behaviours (Table 1), and (3) referral to at least one behaviour change service for a relevant risk behaviour.

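### The single 0.017 level for three primary outcomes is valid, but naming Holm's procedure would give more power at the same 5% family-wise error

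*Protocol article*

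**What the plan says.** Section 2.6.1 of the protocol article defines three co-listed primary outcomes: "The primary outcomes are the proportion of clients who reported receiving elements of the AAR framework of preventive care", namely assessment for all risk behaviours, brief advice for all relevant ones, and referral to at least one service.

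Section 2.7 sizes the trial for them and states that "this sample size will provide 80% power to detect at least a 25% absolute increase in the primary practice change outcomes". The level behind that power figure is given at the end of the same sentence: "with a type 1 error rate of 0.017 to account for multiple testing". It is 0.05/3 to three decimals. Sidedness is not given.

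Section 2.8 specifies a mixed effects logistic model with a service-level random intercept for each primary outcome. It mentions neither a multiplicity procedure nor a small-sample reference distribution. The phrase in section 2.7 is therefore the only multiplicity rule in the document.

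**The concern.** The natural reading of section 2.7 is that each outcome will be judged against a fixed 0.017. That single-step rule is more demanding than 5% family-wise control requires. Once one hypothesis has been rejected at 0.05/3, only two remain, and the smaller of their p-values can be tested at 0.05/2 = 0.025. If that is rejected too, the last can be tested at 0.05. This is Holm's procedure. It needs no assumption about how the outcomes are related.

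The point matters here for two reasons. The trial has 12 services and a stated power of only 80% for a large effect, so there is little to spare. Step-down testing also helps most when several outcomes move together, and the design points that way: one consultation delivers assessment, advice and referral, and section 2.7 plans the same 25-point rise for all three. The earlier single-service trial described in the Introduction reported p-values of <0.001, 0.019 and 0.004 for these elements. Purely as an illustration, since that was a different trial, 0.019 fails a fixed 0.017. Under Holm, <0.001 passes 0.0167, 0.004 passes 0.025 and 0.019 passes 0.05.

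**Working it through.** **Inputs.**
- Section 2.7: 20% in control against 45% in intervention (20% + 25 points), intraclass correlation 0.05, level 0.017.
- Section 2.7: "with a total of 360 clients at each time point (180 intervention group; 180 control group"). The 25% response is already applied, since 0.25 × 720 = 180.
- Section 2.2: "Twelve services will take part in the study", allocated 1:1, so 6 per arm and 180/6 = 30 clients per service.
- Assumed, because not stated: two-sided tests, and between-outcome correlation of 0.3 to 0.6.

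**Step 1: reproduce the stated 80%.**
- Design effect: 1 + (30 − 1) × 0.05 = 2.45.
- Effective sample size per arm: 180/2.45 = 73.5.
- Unpooled standard error: √[(0.20×0.80 + 0.45×0.55)/73.5] = 0.0745.
- Pooled standard error: √[2×0.325×0.675/73.5] = 0.0773.
- Two-sided critical value at 0.017: 2.387.
- Power: Φ[(0.25 − 2.387×0.0773)/0.0745] = Φ(0.88) = 81%.

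The plan's 80% is reproduced.

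**Step 2: power at each Holm threshold.** The standardised effect is 0.25/0.0745 = 3.357. The large-sample column uses the unpooled standard error, which is why it starts near 83% and not 81%. The t column uses 12 − 2 = 10 degrees of freedom.

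| Two-sided level | Large-sample z | t, 10 df |
|---|---|---|
| 0.017 | 83.4% | 68.6% |
| 0.05/3 | 83.2% | 68.3% |
| 0.025 | 86.8% | 75.3% |
| 0.05 | 91.9% | 85.6% |

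Holm's power for any one outcome must lie between the 0.05/3 row and the 0.05 row. Where it falls depends on how often the other outcomes are rejected first.

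**Step 3: Bonferroni against Holm.** Results are from simulated triples of correlated test statistics (200,000 to 400,000 draws per setting).

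| Scenario | Quantity | z: fixed → Holm | t, 10 df: fixed → Holm |
|---|---|---|---|
| All three effective | power per outcome | 83% → 89–90% | about 69% → 79% |
| All three effective | all three significant | 63–68% → 79–82% | 37–43% → 63–67% |
| Two effective | power per outcome | gain of 2–3 points | 68% → 72–73% |
| One effective | power for that outcome | 83% → 83.5% | 68.3% → 68.5% |

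The t ranges for all three significant shift by a few points with the assumed correlation between the three variance estimates. With 8 degrees of freedom, allowing for two LHD terms, the per-outcome figures when all three are effective are about 64% → 75%.

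**Step 4: error control.** Holm's simulated family-wise error was at or below 5% in every setting, as theory guarantees. For the fixed rule the upper bound is 3 × 0.017 = 0.051, which is rounding only.

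**The case against.** The strongest reply is that section 2.7 states a sizing level and does not prescribe an analysis. Section 2.8 does not commit to single-step testing, and 0.05/3 is also Holm's first and strictest step, so sizing at 0.017 is fully compatible with a Holm analysis. The choice may be settled in an analysis plan that is not shown. All of this stands, and it is why the point is an improvement and not a defect. What remains is that the only rule the document gives reads most naturally as a fixed threshold.

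A second reply is that a fixed level gives 98.3% confidence intervals that agree with the decisions, while under Holm such an interval can include no effect for an outcome declared significant. That is a genuine but small cost.

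A third is that equal effects on all three outcomes are not assured: the Introduction also reports an implementation trial that improved only one of 16 preventive care outcomes. This stands as well, and the gain is therefore stated by scenario.

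Two stronger inferences are tempting but unsupported. One is that the 0.017 level leaves the trial with 69% power in place of 80%. The stated 80% reproduces as 81% at 0.017, and the fall to 69% comes from a t reference with few services, which is a separate matter. The other is that family-wise error is inflated because 3 × 0.017 = 0.051. An excess of 0.001 in a conservative bound has no practical meaning.

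**Conclusion.** The point holds as an efficiency improvement. A fixed 0.017 is valid control, and nothing in the document is contradictory or wrong here. Holm keeps the 5% guarantee and never rejects less than Bonferroni at 0.05/3.

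Under the plan's own scenario of a 25-point rise in all three outcomes, the gain per outcome is about 6 points on the large-sample basis and about 10 points with t on 10 degrees of freedom. The gain in the chance of winning all three is about 13–16 points and about 24–26 points respectively. These figures rest on two-sided tests and an assumed correlation of 0.3 to 0.6. The benefit shrinks to 2–5 points per outcome if two outcomes are effective and is essentially nil if only one is. It should not be presented as an unconditional increase.

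**What to change.** In section 2.8, state that the three primary outcomes are tested by Holm's procedure at a two-sided family-wise 5%, with the ordered p-values compared with 0.05/3, 0.025 and 0.05, stopping at the first non-rejection. In section 2.7, keep 0.05/3 and describe it as the conservative level used for sizing. Report 98.3% confidence intervals, with a note that they need not match the step-down decisions exactly.

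If the statistical analysis plan already names Holm, only the wording needs aligning. If it does not, the choice should be recorded before unblinded analysis so that it cannot look data-driven. The cost is one sentence and the small mismatch with the intervals; no extra participants are needed.

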### 2.8. Analysis

Mixed effects logistic regression models will compare the primary outcomes and secondary practice change outcomes (preventive care receipt) between the intervention and control groups at the post-implementation follow-up, adjusting for clustering by service with a service level random intercept. The models will also adjust for potential confounders, including baseline prevalence of preventive care, age, gender, psychiatric diagnosis, and length of time in treatment, as well as LHD as fixed effects. Analyses will be carried out on an intention to treat basis.

In the cohort sub-study, generalised mixed effects regression models will determine the change over time (baseline to 9-month cohort follow-up) in the intervention compared to control participants in the measures relating to client behaviour change: smoking status (yes/no), serves of vegetables per day, serves of fruit per day, number of standard alcohol drinks per week, minutes of moderate and vigorous physical activity per week and body mass index (BMI). Models will adjust for clustering by service and potential confounders as well as LHD. Descriptive analyses will be used to report the remaining measures.

### 2.9. Economic Analysis

To provide a measure of resources required to develop and implement the new model of care, the cost of the intervention will be prospectively measured and valued from a health service delivery perspective. Cost-effectiveness analysis will compare the relative costs and effect of the intervention to usual care delivery in terms of trial primary outcomes. Sensitivity analyses may be conducted to determine impact of clinician salaries and COVID-19 (e.g., changes in the number of hours worked per week). Budget impact analysis will estimate the affordability of the intervention, calculating real-world implementation costs in financial terms, considering the specific contexts of each health district.

